## Trial design

This study has been approved by the NSPCC Research Ethics Committee R/15/67and is funded by the Department of Education in Northern Ireland. The Keeping Safe trial is designed as a two-arm cluster randomised control trial using a wait-list control group with a 1:1 allocation. The unit of analysis will be the school but analysis will also be conducted at the level of the individual, while taking into account the nesting effects of class and school.

### Study setting

This trial seeks to provide the evidence to inform Department of Education Northern Ireland policy regarding the development of prevention education across the Northern Ireland school system. In order to ensure a representative sample and address religious segregation/equality issues specific to Northern Ireland, schools will be recruited from across the five regions of the Education Authority in Northern Ireland and will take account of the four main School Management Types (Roman Catholic Maintained, Controlled, Grant Maintained Integrated, and Irish-Medium).

### Eligibility criteria

#### Inclusion criteria

Children aged four to 11 years old attending mainstream sector primary school in Northern Ireland whose school has accepted the invitation to take part in the RCT and whose parents have provided consent for their participation.

#### Exclusion criteria

Children attending special sector primary schools in Northern Ireland.Children aged four to 11 years old attending mainstream sector primary school in Northern Ireland whose school has not been invited/ rejected the invitation to take part in the studyChildren aged four to 11 years old attending mainstream sector primary school in Northern Ireland whose school has accepted the invitation to take part in the study and whose parents, or they personally, have not provided consent for participation.

### Randomisation

Randomisation will be carried out by an independent consultant and will be conducted using a computer-generated list of numbers. The allocation will be emailed to the Principal Investigator who will then email individual notifications to schools within a designated timeslot on 1 day. Entire schools will be randomised to the intervention or wait-list control following baseline data collection with stratification by School Management Type and school enrolment size with a 1:1 allocation. This will be achieved as follows:The schools will be sorted by management type and, within management type, by enrolment numbersSchools will be assigned to pairs starting from the top of the sorted list. For example, the two largest catholic maintained schools will be assigned to ‘Pair 1’; the third and fourth largest to ‘Pair 2’ etc.A random number between 0 and 1 will be assigned to each school (the random number being generated within SPSS)Within each of the pairs the school with the smallest random number will be assigned to the intervention group and the other school from the pair will be assigned to the wait-list control group

### Intervention: Keeping safe

*Keeping Safe* is a comprehensive multi component ‘Whole-School’ programme designed to teach children aged four to 11 years old how to keep safe from all forms of maltreatment, including: neglect, sexual abuse carried out online or using digital technology, abuse perpetrated by other children, and bullying. This is premised on identified priority gaps in existing programmes [12, 13, 22, 26, 33, 37] and the fact that key messages have applicability across multiple forms of maltreatment [28, 47]. Table 1 outlines the key themes and messages taught to children and tailored to their age and developmental needs. For example in relation to sexual abuse, children are taught how to recognise unsafe situations and grooming behaviours such as the use of bribes and threats. Keeping Safe also teaches children that people they know and love can perpetrate abuse which is important as the majority of children will be abused by people they know rather than strangers [13]. Moreover, while the programme employs a range of methods to teach knowledge and understanding (for example books, role play and animations), significant time and content is devoted to skill development and practice; a key component of effective prevention programmes [22, 28, 41, 48].

**Table 1 Tab1:** Overview of the Keeping Safe Programme: Themes and examples of key messages by age group

Theme description and Term	Examples of key messages for children by age-group
Healthy Relationships in Term 1: teaches children to recognise what a healthy relationship looks like (online or face to face), between adults at home, peers or friends. This theme addresses bullying behaviour and most forms of abuse.	4-6 yrs. the names of feelings, their hands are not for hurting, that no one has the right to hurt them, what to do if someone hurts them, what to do if they are worried about someone else being hurt.
	6-8 yrs. they have the right to be in a happy and caring environment, what a good friendship should look like, that it’s okay to say no to a friend, what to do if they feel hurt by anyone (even if it is an adult).
	8-11 yrs. the importance of having respect for others, the different types of bullying behaviour, the reasons for it and strategies for dealing with bullying, what cruelty is and how we can stop it, the problems that can occur with online friendships, how to recognise an unhealthy relationship, what domestic abuse is and know that it is wrong.
My Body in Term 2: focuses on sexual abuse. It teaches children to recognise when they don’t feel safe by explaining the difference between appropriate and inappropriate touch, the difference between secrets and surprises and how to identify if they are being tricked into doing something unsafe.	4-6 yrs. what private means and know the proper names for body parts, that we don’t share private parts, the difference between appropriate and inappropriate touch, they have the right to say no if their body gets a feeling that they don’t like, the difference in secrets and surprises.
	6-8 yrs. that privates are not for sharing, that their body belongs to them, to talk about secrets that upset them even if it involves someone they or their family know very well, no one should make them do things that they don’t want to, they will know how to say no, to recognise bribes and threats and know what to do.
	8-11 yrs. that their body belongs to them and they are entitled to privacy, that private areas should never be shared, the potential dangers with sharing photos online, to be able to identify the four main forms of abuse (neglect, sexual, physical and emotional), the problems some people face in telling about abuse.
Being Safe in Term 3: encourages children to talk about their feelings. They are taught how to seek help from a trusted adult when they don’t feel safe or realise what has happened to them is wrong or abusive. Children are also taught how and when to talk to safe adults and to keep telling until they get help.	4-6 yrs. what safe means and to explain the feelings they get when they are safe, identify situations that are safe and not safe, to tell someone if they are not feeling safe, that they should talk about worries, identify their safe adults, the importance of asking for help from an adult while online.
	6-8 yrs. recognise different body signs when they feel unsafe, how to keep themselves safe online, the importance of staying with a safe adult in public places, safe people to ask for help from in different situations, , not to make judgements based on appearances alone.
	8-11yrs. the difference in needs and wants, they have a right to feel safe and secure, how their body reacts when they are angry or feel threatened, what is safe to share online and offline, to tell an adult if they are being asked for personal information online or being asked to meet someone they have met online, what is meant by cyber bullying, how and why it happens and how to deal with it, to educate younger children in the school about ‘Keeping safe’.

The ‘Whole- School’ model adopted by Keeping Safe is increasingly advocated in policy documents [1, 2, 49] yet is relatively untested and lacks evidence of effectiveness [30]. This model supports the development of Keeping Safe as a multi-component programme with key components targeted at children and their parents as well as teachers and other whole school staff.

Teaching and learning resources seek to build the capacity of school staff to teach and reinforce messages through the formal and informal curriculum. These were designed to integrate into the existing ‘Personal Development & Mutual Understanding’ statutory component of the Northern Ireland Curriculum in primary schools and to the wider life of the school [30, 34]. The classroom based materials developed across three themes of healthy relationships, my body and being safe, include a wide range of materials including 63 lesson plans (nine for each class group per year) designed to teach key messages incrementally as the children progress through the 7 years of their primary school education from Primary one to Primary seven. This approach of providing curriculum support materials that are tailored to the age and developmental abilities of the children and build on prior learning is associated with effective prevention programming [29, 30, 48]. In practice, school leaders will deliver a prepared assembly, one of twelve available, to introduce the theme for the term. Each teacher will then deliver three age appropriate lessons to their class and ask the children to complete the accompanying homework with their parents or carers. The structured programme provides teachers with sufficient time and multiple opportunities to revisit and reinforce key messages; important elements of effective programmes [48].

Parental involvement, also associated with effective programmes [47, 50–53] is an integral component of Keeping Safe. Parents are engaged in directed homework activities with their children and are encouraged to attend a structured information session and expert workshops seeking to build their knowledge, skills and confidence to reinforce their children’s learning at school. Training and support for teachers and whole school staff, also an important component of the Keeping Safe programme [26, 30, 54], involves a blended package of training aimed at building the capacity of school leaders, teaching and non-teaching staff to teach and embed the programme in all aspects of school life.

### Wait list control group

The wait-list control group will continue to receive the Northern Ireland Personal Development & Mutual Understanding curriculum as usual for the duration of the trial. They will be advised to continue and record delivery of other related programmes/ resources already embedded in school practice, and asked not to take on any new programmes of this nature for the duration of the trial. They will participate in three rounds of data collection and will receive the programme once the evaluation ends.

### Recruitment and participants

The trial will adopt a random stratified sampling approach to school recruitment. The sample will be stratified according to the four main School Management Types (Roman Catholic Maintained, Controlled, Grant Maintained Integrated, and Irish-Medium) and the five regions of the Education Authority in Northern Ireland.

A total random sample of 120 primary schools will be identified for recruitment purposes (see Fig. 2). This will include a main sample of 80 schools and a replacement sample of 40 schools. If a school from the main sample declines their invitation, a matched replacement school will be invited to attend in their place. Additional samples will be identified as required until recruitment targets are met. It is envisaged that approximately 150 children will complete questionnaires per school at each data collection timepoint. The average enrolment number is 200 children per school but only a minority of children in the youngest primary year groups (Primary One and Primary Two) will take part in the study. Further to this, it is also anticipated that there will be absences among older year groups.

**Fig. 2 Fig2:**
[figure not shown]
Flow of participants in Keeping Safe RCT

A member of the school leadership team will be invited to attend an information session about the programme. These sessions will include presentations from the project team on the programme content and delivery, and the RCT evaluation. School leaders will be provided with school planning resources including school development plan inserts, school calendars outlining key dates for programme implementation and evaluation as well as sample surveys/ programme resources to assist their informed decision-making regarding participation. To maximise recruitment, the project team will also follow up with phone calls and provide additional information and support/meetings as and if required. School leaders will be asked to consult their stakeholders and provide consent for their school to participate in the trial. They will then be asked to sign a Memorandum of Understanding that formalises expectations and responsibilities of schools and the project team for the conduct of the trial. Schools will then be asked to distribute evaluation information packs and consent forms to the parents of every child in their school.

### Sample size

The sample size calculation was based on an assumed intra-class correlation coefficient of 0.2, as observed in similar school-based preventative education programmes [29]. The calculation was also based on the primary outcomes of the study, i.e. changes in children’s knowledge, understanding, self-efficacy and proxy skills to keep safe from all forms of abuse. Other studies concerned with preventing sexual abuse that have used a cluster randomised design have reported an average increase of 0.63 standard deviations (ICC = 0.2) for knowledge of sexual abuse concepts, and an average increase of 0.60 standard deviations (ICC = 0.2) for proximal measures of safety skills (i.e. the What If Situations Test) in the intervention group. Programmes with a focus on domestic abuse prevention have reported increases of 0.3–1.3 standard deviations for knowledge of domestic abuse concepts in the intervention group [30]. These studies have also reported an odds ratio of 2.95 in relation to disclosures of abuse [29] while others have reported an odds ratio of 1.10 in relation to reductions in bullying victimisation and perpetration [40].

Power calculations for the current study indicate that approximately 40 schools are required in each arm of the study to detect a minimum detectable effect size of 0.19 standard deviation with 80% power and 95% significance. This will also allow for a minimum detectable percentage point difference of 2.7 for an outcome that is rare in the control group, at around 5% (i.e. disclosure of abuse).

There are several assumptions behind the calculations:The average number of completed surveys per school will be around 150 per timepoint. (The average enrolment number is 200 per school, but the very youngest year groups will not all be included, and amongst older year groups there will be absences);It will prove feasible to track the responses from the same pupils over time. The assumption is that for around 50% of the surveys at follow-up, we will have matched baseline data;For single year group analysis, the average sample size per school will be 30 completed surveys per timepoint;The intra-class correlation coefficient is assumed to be 0.2. This is a value typical for school based studies [29].

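### The minimum detectable effect of 0.19 SD does not follow from the printed inputs: unadjusted they give 0.28–0.29 SD, and 0.19 needs a school-level baseline correlation of about 0.75 that is not stated

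*Protocol article*

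**What the plan says.** The Trial design section describes a "two-arm cluster randomised control trial using a wait-list control group with a 1:1 allocation", with the school as the unit of randomisation. The Sample size section of the protocol article states: "approximately 40 schools are required in each arm of the study to detect a minimum detectable effect size of 0.19 standard deviation with 80% power", at 95% significance. It adds a second figure, a detectable difference of 2.7 percentage points for an outcome at about 5% in the control group.

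The same section lists the assumptions behind these figures:

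- "The average number of completed surveys per school will be around 150 per timepoint".
- "The intra-class correlation coefficient is assumed to be 0.2".
- "The assumption is that for around 50% of the surveys at follow-up, we will have matched baseline data".
- For analyses of a single year group, 30 surveys per school.

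It says the calculation concerned changes in the children's outcomes. It gives no correlation between baseline and follow-up, no R² and no formula. Planned analyses describes longitudinal multilevel models that include the baseline occasion.

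**The concern.** In a school-randomised trial with an ICC of 0.2, precision is governed almost entirely by the number of schools. Forty schools per arm at that ICC looks too few for 0.19 SD, whatever the number of pupils surveyed. If the printed figure is wrong, or true only under an input the reader cannot see, the article overstates the sensitivity it has documented for all the child score outcomes. The trial is meant to inform education policy. A non-significant result, or an estimate near 0.2 SD, could then be judged against a precision that the stated inputs do not deliver.

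**Working it through.** **Inputs, from Trial design and Sample size.** k = 40 schools per arm, m = 150 surveys per school, ICC = 0.2, power 80%, 5% significance. Sidedness is not stated, so two-sided is taken: 1.960 + 0.842 = 2.802.

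**Attempt to reproduce 0.19.**

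- Formula: MDES = 2.802 × √[(2/k) × (ICC + (1 − ICC)/m)].
- ICC + (1 − ICC)/m = 0.2 + 0.8/150 = 0.2053.
- Standard error = √(0.05 × 0.2053) = 0.1013.
- MDES = 2.802 × 0.1013 = **0.284 SD**. It is 0.287 with t on 78 df, and 0.291 with t on 39 df (treating the school pairs as the unit).
- The same by design effect: 1 + 149 × 0.2 = 30.8, so the effective size is 6000/30.8 = 194.8 per arm.
- Power at 0.19 SD = Φ(0.19/0.1013 − 1.960) = **0.466** (0.457 with the noncentral t).
- Schools needed for 0.19 SD unadjusted: 435 × 30.8/150 = 89.3 per arm, against 40 stated.

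**Other readings of the printed inputs, unadjusted, 40 schools per arm, ICC 0.2.**

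| Variant | Detectable effect (SD) |
|---|---|
| m = 30 (single year group) | 0.298 |
| m = 75 (only the matched half) | 0.288 |
| m = 200 (full enrolment) | 0.283 |
| m unlimited: 2.802 × √(0.05 × 0.2) | 0.280 |
| m = 150, one-sided 5% | 0.252 |

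The between-school term alone gives 0.280, so no survey count can produce 0.19.

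**What would produce 0.19 with 40 schools per arm and m = 150.**

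- Equal R² at both levels: 1 − (0.19/0.2839)² = 0.552, a correlation of √0.552 = 0.74 (0.563 and 0.75 with t).
- R² between schools only: 0.567.
- R² within schools only: even R² = 1 leaves 0.280.
- No covariates, smaller ICC: about 0.086, against the stated 0.2.

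**Sensitivity to an assumed R² at both levels (m = 150).** Detectable effect = 0.2839 × √(1 − R²).

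| Assumed R² | Detectable effect (SD) | Power at 0.19 SD |
|---|---|---|
| 0 | 0.284 | 47% |
| 0.25 | 0.246 | 58% |
| 0.50 | 0.201 | 76% |
| 0.55 | 0.190 | 80% |

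**Companion figure.** With an effective size of 194.8 per arm, the detectable difference from 5% is about 8.1 points, not 2.7. With the R² or the ICC that rescues 0.19, it is still about 5.0 points. To reach 2.7 points at m = 150 the ICC must be about 0.025. No single set of inputs tried gives both printed figures.

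**Effects the article cites.** Unadjusted power is 84% at 0.30 SD and above 99.9% at 0.60 SD.

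**The case against.** The strongest reply is that 0.284 SD and 46% describe an analysis the trial does not plan. The article lists baseline matching as an assumption, speaks of changes in outcomes, and plans longitudinal models. Matching has little purpose in a sample size calculation unless baseline enters it. An ordinary, uncentred pupil baseline score also carries school differences, so it removes between-school variance as well. Taking 75 matched pupils per school and an assumed correlation of 0.75 at both levels gives 0.2875 × √(1 − 0.5625) = 0.190 SD. At an assumed 0.60 it is 0.230, at 0.70 it is 0.205 and at 0.80 it is 0.173. A journal article also condenses a fuller protocol, so the absence of a correlation does not show that none was used.

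Most of this stands. A reader might infer that matched baselines cannot close the gap. That is true only if they explain variance within schools and none between them. A reader might also infer that 0.19 is impossible with 40 schools per arm, and the documents do not support that either.

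The reply does not make the printed figure derivable. The article prints a result together with the assumptions behind it, and the input that would have to cut the variance by more than half is not among them. This is a mismatch between a stated result and its stated inputs, not a detail left to the analysis plan. Nor does baseline adjustment at the level that rescues 0.19 rescue the 2.7 points.

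**Conclusion.** The concern holds in a limited form. From the printed inputs the unadjusted detectable effect is 0.28–0.29 SD, about 50% larger than 0.19 (0.284/0.19 = 1.49), and unadjusted power at 0.19 SD is about 46%. The figure of 0.19 is attainable only as a baseline-adjusted one, under an unstated and demanding condition: about 55% of the between-school variance removed. The figure of 2.7 points is likewise not reproduced at ICC 0.2.

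These results assume a two-sided 5% test, equal school sizes and an ICC of 0.2 for every outcome. The R² values and correlations are assumptions of this review.

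A reader might conclude that the trial as designed has less than even odds of detecting 0.19 SD. The documents do not support that, because 46% is power without baseline adjustment and the planned models use baseline; with an assumed R² of 0.50 it would be 76%. A reader might also conclude that the trial is too small for its purpose. That is not supported either: the cited standardised effects, from 0.30 SD upwards, are detectable with at least 80% power even unadjusted. The practical consequence is confined to how results near 0.2 SD are read.

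**What to change.** Either of two corrections to the Sample size section would do:

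1. State the detectable effect as about 0.28–0.29 SD unadjusted, with 0.25 and 0.20 SD shown for assumed R² of 0.25 and 0.50.
2. Keep 0.19 SD, label it as baseline-adjusted, and state the formula and the school-level correlation it needs (about 0.74–0.75). In that case, make sure the primary model uses baseline in a way that removes between-school variance, for example through an uncentred pupil baseline score or the school-mean baseline.

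In both cases, state whether the test is two-sided, and restate the figure of 2.7 points or give the ICC and method behind it.

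The cost is a rewording and, under the first option, a less favourable headline figure. The second option needs at most one extra model term from data already collected. No additional schools are required.

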### Blinding

While it is not possible to blind trial participants in schools or programme facilitators delivering the Keeping Safe training to schools, outcome data will be obtained through self-report measures for teachers, parents and Primary three to Primary seven children thus reducing potential outcome assessor bias. Agency volunteers who will be collecting one to one interview data from Primary one and Primary two children will be blinded to school allocation status. Data processors and the trial statistician will also be blinded in this regard.

